#### **8.4.9 Daily logging of symptoms and confounders in Ava COVID-RED app**

Subjects will be asked to record any experienced symptoms and potential confounders (e.g., alcohol consumption) daily within the Ava COVID-RED app. Symptoms can be recorded in-app for up to 7 days after each date.

#### **8.4.10 Nightly wearing & routine syncing of the Ava bracelet**

Subjects will be instructed to wear the Ava bracelet each night and synchronise it with the Ava COVID-RED app each following day for the complete follow-up. Throughout the study, subjects will be able to observe and track changes in their resting heart rate, breathing rate, skin temperature, sleep, and heart rate variability as recorded by their Ava bracelet.

#### **8.4.11 Receive algorithm-based health indicator**

During follow-up, subjects will be informed by the Ava COVID-RED app whether the algorithm has detected symptoms and/or changes in physiological parameters potentially indicative of a COVID-19 infection. Following onboarding instructions provided by the study team, subjects will then be expected to seek testing for SARS-CoV-2. Algorithms will be used to assess the risk of potential SARS-CoV-2 infection. In the control condition, the algorithm is solely reliant on symptom data entered by the subject during the study and background medical information collected at registration. In the experimental condition, the algorithm is additionally reliant on physiological data collected from the Ava bracelet. If subjects are given a red-light indicator (significant changes in biophysical parameters have been detected or symptoms that meet the RIVM criteria have been reported), they will be advised to seek testing for SARS-CoV-2 infection.

#### **8.4.12 Testing for presence of SARS-CoV-2 virus**

Subjects will receive specific instructions at the start of the study to always contact the GGD for SARS-CoV-2 virus testing when receiving a red-light indicator and only request for self-sampling kits for the central laboratory PCR testing service when turned down for testing by the GGD in line with the criteria applicable at that moment in time.

If subjects cannot be tested through the GGD because they do not qualify as per the current RIVM testing guidelines, they will be instructed to contact the study team and request a self-sampling PCR kit. The kit will be sent to them as soon as possible including instructions. Subjects will be instructed to take the sample and use the pre-addressed medical envelope with prepaid postage to send the sample to the central laboratory within 24 hours. The samples will be processed and stored at the central laboratory on the day of receipt. Results will be communicated back to the subjects and any positive results will be reported to the GGD.

#### **8.4.13 Logging any SARS-CoV-2 test results and vaccination in Ava COVID-RED app**

Subjects will be instructed to log results from a SARS-CoV-2 test, independent of where the test was obtained, directly into the Ava COVID-RED app via the Daily Symptom Diary. Results from the serum antibody testing will also be provided by the central laboratory directly to the primary investigators. If a test result is negative, the subject will continue with the study procedures as planned. If the test result is positive, the Ava COVID-RED app will continue in a COVID-positive mode during which the subject will remain in the study and will

still be asked to record symptom data and wear/sync the bracelet. However, the subject will not receive any further algorithm-based indicators; instead, they will see a constant message on their Ava COVID-RED app home screen suggesting they seek additional medical care if their symptoms worsen or fail to improve.

When subjects receive any kind of vaccine (including any COVID-19 vaccine), they can log this in the Ava COVID-RED app and provide details in an unstructured open-text response field following the prompt, “If you received a new vaccine within the prior 24 hours, please specify which one: [Vaccine]”. Subjects that have received a COVID-19 vaccine during follow-up will continue using the app as instructed at onboarding and should seek testing for SARS-CoV-2 when receiving the red light indicator as described above.

#### **8.4.14 Periodic completion of survey**

Every two weeks, a survey will also be sent to obtain more specific details on the testing procedures, epidemiological, household, occupational data and behaviour of the subjects. These surveys will allow the subject to self-report details on if they took a SARS-CoV-2 virus test, where they took it, how long they waited after receiving an in-app indicator before contacting the GGD, the time until they took their own sample and sent it to the central laboratory (if applicable), the type of test they took, how long it took them to receive their test results, and the result itself. These characteristics will also give a sense of the risk for SARS-CoV-2 infection that a subject has and can reveal important epidemiological relations as detailed in the study objectives. In addition, specific structured questions will be asked to subjects if they received a COVID-19 vaccine, including which dose (i.e., first or second) and from which manufacturer.

#### **8.4.15 Regular completion of hospital episodes and adverse device effects (ADEs)**

Subjects will regularly be asked to self-report possible hospital episodes related to COVID-19 (once every two weeks) and adverse device effects (ADEs) (once every month). For hospital episodes, questions on the dates and name of the facilities will be included.

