### 2.2 Secondary Objective(s):

1. To assess the health economic utilization of a wearable device and mobile application as measured by endpoints such as:
  - a. Number of tests for suspected SARS-CoV-2 infections
  - b. Number of hospitalizations
  - c. Number of ICU events
  - d. Number of days requiring breathing support (e.g. oxygen and/or ventilation)
2. To determine the incidence of SARS-CoV-2 infection during the study
3. Identify which features of the Ava bracelet and Daily Symptom Diary are the most predictive features
4. Assess the independent predictiveness of an algorithm derived from physiological data gathered by the Ava bracelet in addition to self-reported daily symptom data
5. To assess the time from algorithm indication to symptom onset in the subject
6. To assess the time from algorithm indication to testing of the subject
7. To determine how taking antipyretic medication affects physiological parameters among subjects using the Ava bracelet and Daily Symptom Diary
8. To determine how self-reported vaccinations cause changes in biophysical parameters from subject's given baseline measurements
9. To correlate the longitudinal symptoms reported by study subjects confirmed to have COVID-19 with changes over time in their physiological data
10. To characterise longitudinal symptoms and recovery dynamics reported by the study subjects to the presence or absence of lab-confirmed SARS-CoV-2 infection
11. To assess the adherence to daily symptom diary completion and Ava bracelet wearing and synchronising over time

12. To determine the time necessary to establish baseline physiological parameters per subject in the Learning Phase of the study
13. To determine if retrospective identification of the moment of potential SARS-CoV-2 infection is possible for subjects who are seropositive at the end of a period but were negative at baseline and did not receive an alert to get tested during the study
14. To determine the rate of breakthrough and asymptomatic COVID-19 infections among vaccinated individuals
15. To assess the influence of self-reported COVID-19 vaccinations on compliance to study procedures

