#### 8.1.2 Secondary study parameters/endpoints (if applicable)

Additional endpoints will be collected for analysis of the secondary objectives as listed in Section 2.

*Study condition compliance (collected with Ava COVID-RED app)*

- Duration of Ava bracelet use (amount of days between first day of synchronised data and last day of synchronised data)
- Duration of daily symptom diary use (amount of days between first day completed symptom data and last day completed symptom data)
- Compliance rate: percentage of days (as compared to duration of use) that Ava bracelet was worn and synchronised.
- Compliance rate: percentage of days (as compared to duration of use) that symptoms were entered into the Daily Symptom Diary of the Ava COVID-RED app

*Longitudinal characteristics of study population (collected with Ava COVID-RED app)*

- Number/percentage of non-antipyretic and antipyretic medication days
- Number and type of vaccination events
- Number/percentage of days with alcohol consumption
- Number/percentage of days with recreational drug usage
- Number/percentage of days with period (menstruating women only)
- Number of pregnancy events (menstruating women only)

*Overall incidence of SARS-CoV-2 (collected through self-reporting of PCR/antigen test results in the Ava COVID-RED app and serology results)*

- SARS-CoV-2 cumulative incidence by condition and by stratum

*Healthcare Resource Utilization (collected throughout the study through bi-weekly surveys in COVID-RED web portal, structured interviews, and Ava COVID-RED app)*

- Number of COVID-related contacts from subjects to their general practitioner (GP)
- Number and duration of COVID-related hospitalization episodes
- Number and duration of COVID-related intensive care unit (ICU) episodes
- Number and duration of COVID-related supported breathing intervention
- Number and percentage of subjects with each reported medication used during hospitalization (WHO Drug Dictionary [WHO-DD])

*COVID-19 Testing (collected throughout the study through bi-weekly surveys in COVID-RED web portal and Ava COVID-RED app):*

- Number of tests conducted by GGD
- Number of provided PCR kits used
- Number of tests conducted due to red-light indicator of Ava COVID-RED app
- Time between first recommendation for testing and contact with GGD
- Time between first recommendation for testing and contact with study team for PCR sample kit

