## **8.7 Follow-up of subjects withdrawn from treatment**

To ensure the number of subjects lost to follow-up is kept to a minimum, the subject will be asked to provide contact details of a back-up person upon study entry. In the event that a subject is considered lost to follow-up, the investigator may decide to contact this back-up person to enquire if the subject is able to re-join the study. A specific study procedure will be available to support this process.

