### 10.2 Primary Analysis of Primary Endpoint(s)

The primary analysis of the primary endpoint will compare the performance of the algorithm applied in each study condition to detect if subjects were ever infected during Period 2. This analysis will be performed on both the Intention-to-treat and Efficacy analysis sets, within each period and stratified per risk group. For the subjects within each study condition, the daily prediction of possible SARS-CoV-2 infection and the results of PCR/antigen and serology tests will be summarized over the whole period per subject to determine (1) if a subject was ever judged to have a high risk for a potential SARS-Cov-2 infection (i.e. received a red-light indicator from the Ava COVID-RED app), and (2) if a subject was ever confirmed to have a SARS-CoV-2 infection by PCR/antigen or serology testing. For this comparison, parameters such as sensitivity, specificity, positive predictive value, and negative predictive value will be calculated.

To confirm whether a subject was ever infected in Period 2 with SARS-CoV-2, the serology status at the end of Period 2 for each subject still alive at that time will be used as the gold standard. Those with a previous positive test result will be excluded from the analysis. For subjects not alive at the end of Period 2, the status of available SARS-CoV-2 virus tests during Period 2 will be used (positive at any time) and for those without any test results, a physician diagnosis during Period 2 will be accepted provided there was a supportive lung CT scan used. All other subjects will be summarized for transparency but excluded from the estimation for sensitivity, specificity, positive predictive value and negative predictive value.

The following quantities are needed for these statistics:

- **Predicted condition positive:** The total number of subjects that obtained a red-light indicator from the Ava COVID-RED app at least once during Period 2.
- **Predicted condition negative:** The total number of subjects that never obtained a red-light indicator from the Ava COVID-RED app during Period 2.
- **Condition positive:** The total number of subjects who tested positive at least once using SARS-CoV-2 virus testing during Period 2 OR who had a positive serology test at the end of Period 2.
- **Condition negative:** The total number of subjects who never tested positive for the SARS-CoV-2 virus during Period 2 AND who had a negative serology test at the end of Period 2.

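### Hospital, ICU, breathing-support and GP use is captured only if the subject reports it and thinks it COVID-related, a belief the red light can influence; no route is defined for subjects who die or fall silent

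*Protocol*

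**What the plan says.** Secondary objective 1 (Protocol 2.2) reads "To assess the health economic utilization of a wearable device and mobile application as measured by endpoints such as". Its list includes "Number of hospitalizations", ICU events and days of breathing support, with no limit by cause.

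Section 8.1.2 narrows these to COVID-related use: "Number of COVID-related contacts from subjects to their general practitioner (GP"), "Number and duration of COVID-related hospitalization episodes", and ICU and supported-breathing episodes limited in the same way. The data route is "collected throughout the study through bi-weekly surveys in COVID-RED web portal, structured interviews, and Ava COVID-RED app".

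The subject starts every step. Section 3.8 (item 5) describes reporting by subjects of GP or hospital contacts linked to SARS-CoV-2. In 8.4.15, "Subjects will regularly be asked to self-report possible hospital episodes related to COVID-19 (once every two weeks"). Section 8.4.16 places the structured interview after the subject's report and holds it with that subject.

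For subjects who go silent, 8.7 says "the investigator may decide to contact this back-up person to enquire if the subject is able to re-join the study". Section 12.1 mentions physician interviews in lost-to-follow-up scenarios without giving their content or respondent. Section 10.2 has its own rule "For subjects not alive at the end of Period 2", and 10.5 names survival status at the end of follow-up as an endpoint.

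**The concern.** Two filters stand before an episode is counted: the subject must answer the survey, and must think the episode was COVID-19.

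The second filter is close to what the trial varies. A red light tells the subject that the data may point to COVID-19 and suggests testing or medical advice (3.4). The rule behind it differs by condition (3.3), and 10.5 compares these endpoints within each period. If the alert changes the label, the count can differ between conditions when actual use does not. The interview can remove a wrong report but cannot find one never made.

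The first filter bears on the most severe cases. A subject who dies or never resumes answering supplies no hospital, ICU or ventilation data, and no section assigns the task of finding out. Section 10.2 nevertheless needs to know who was alive at the end of Period 2, and accepts a physician diagnosis supported by CT for some who died.

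An analysis plan can handle incomplete data only if the plan for collection shows what is missing. Here the missing episodes leave no trace.

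**Working it through.** **1. Is there another route?** The protocol gives no sample size, power or expected count for healthcare use, so there is no figure to reproduce. The check is a trace of every section that could supply these data.

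- 3.8, 8.1.2, 8.4.15: subject report, limited to COVID-related contacts.
- 8.4.16: interview, triggered by the subject's report of a hospital episode.
- 9.2.1 and 9.2.2: adverse-event and SAE recording is limited to device-related effects, so ordinary all-cause reporting of admission and death is absent.
- 12.1: source data are declared inapplicable. No record linkage, record review or proxy report of care is described.
- 3.6: serology finds missed infections, not missed care.
- 8.7 and 12.1: back-up contact and lost-to-follow-up interviews, neither set up to collect care data.

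**2. Can the label depend on condition?** Under 3.4 and 8.4.11, reported symptoms meeting the RIVM criteria give a red light in both conditions, and 4.4.2 assumes that both algorithms flag a symptomatic subject at the same time. For subjects who log such symptoms, alerts should be nearly equal. The remaining difference comes mainly from bracelet-based alerts in the experimental condition, in subjects without symptoms or who did not log them. The dependence is thus possible but partial. It is an inference from the design, not something the protocol states.

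**3. What would unequal capture do?** Illustration only.

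Inputs from the protocol: n = 10,000 per condition (4.4.1); two-sided 0.05 (section 10); Table 2 proportions 5,427/180,182 = 3.01% (week 36) and 23,264/223,274 = 10.42% (week 40), used as infection proportions as the protocol does for its power tables.

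Assumed inputs: hospitalisation in 1–5% of infected subjects, GP contact in 20–50%, and the capture pairs below. True use is equal in both conditions.

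Formulas: p = infection × risk of use × capture; SE = √[p₁(1−p₁)/n + p₂(1−p₂)/n]; chance of a significant difference towards the better-captured condition = Φ(|p₁−p₂|/SE − 1.96). With equal capture this chance is 2.5%.

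| Capture | False ratio | Hospital episodes | GP contacts |
|---|---|---|---|
| 95% v 90% | 0.95/0.90 = 1.06 | 3–5% | 5–14% |
| 95% v 80% | 0.95/0.80 = 1.19 | 4–13% | 14–76% |
| 90% v 70% | 0.90/0.70 = 1.29 | 5–21% | 23–96% |

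Worked case (GP, 20%, 3.01%, 95% v 80%): p₁ = 0.0301 × 0.20 × 0.95 = 0.00572; p₂ = 0.0301 × 0.20 × 0.80 = 0.00482; SE = 0.00102; Φ(0.88 − 1.96) = 0.14.

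True hospital episodes per condition and period run from 10,000 × 0.0301 × 0.01 = 3 to 10,000 × 0.1042 × 0.05 = 52. For admissions the harm is therefore mainly a biased, imprecise estimate; for GP contacts it could also be a false positive.

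**4. Silent subjects.** If a share f of hospitalised subjects never answers and their stay is k times that of the others, the share of days lost is fk/(fk + 1 − f). With f = 0.05, k = 1 this is 0.05; with f = 0.20, k = 3 it is 0.60/1.40 = 0.43. Both f and k are assumptions. Nothing in the protocol suggests that f differs by condition.

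**The case against.** The other side has real weight.

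- **Alerts.** A reader might infer that one condition alarms more and so must collect more COVID-labelled contacts. The protocol does not support that. Reported RIVM symptoms, fever included, give a red light in both conditions, so a large alert gap among febrile subjects who keep the diary does not fit its rules. This stands, and leaves direction and size open.
- **Admissions.** A hospital can diagnose COVID-19 without the app. This stands; the concern is weaker for hospital and ICU episodes.
- **Real effect.** Section 3.4 advises medical contact after a red light, so a GP visit it truly prompts is utilisation that objective 1 sets out to measure. This stands. But the design cannot separate such visits from visits that merely carry a different label.
- **Safeguards.** The survey asks about possible episodes, and medical professionals hold the interview. Both help only with episodes the subject already suspects.
- **Silent subjects.** A reader might infer that the back-up person is the sole fallback, or that the gravest cases will be filed as loss to follow-up or poor compliance. Section 12.1 mentions lost-to-follow-up interviews, 8.5.1 lists death as a separate withdrawal reason, and a subject who recovers may report later. Neither inference is supported. What stands is that none of these routes has defined care content.
- **Scope.** Restricting to COVID-related use is legitimate in this trial, and 2.2 lists its measures only as examples, so 2.2 and 8.1.2 do not truly conflict. The difficulty is who applies the restriction, and when.

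**Conclusion.** The point holds as a weakness in how secondary objective 1 is ascertained. Reporting and attribution both begin with the subject, the red light can influence attribution, and the red-light rule differs by condition. Capture could differ by condition, chiefly for GP contacts and less for admissions. The false ratios of 1.06 to 1.29 rest wholly on assumed capture gaps; they show what such gaps would do, not that they exist.

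The lack of a defined route for care data and vital status in subjects who die or stop responding is a second, smaller gap. It mainly costs completeness: 5% to 43% of days under the assumed range.

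The primary sensitivity and specificity analysis is hardly touched; 10.2 uses vital status only to choose the reference standard. The survey change is worth making because episodes never asked about cannot be recovered at analysis.

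**What to change.** **Survey (8.4.15 and the GP item under 3.8 and 8.1.2).** In the existing two-weekly survey, ask for any hospital admission, and any GP contact for respiratory or febrile illness, whatever the subject believes the cause to be.

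**Attribution.** Assign COVID-relatedness afterwards from virus-test and serology dates, by staff masked to condition; under 8.2 the sponsor and investigator know the sequence. Because red lights also prompt virus testing, show the counts regardless of cause beside the COVID-related ones.

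**Section 8.7.** Extend the purpose of the existing back-up contact to vital status and hospital admission, and say what the lost-to-follow-up interviews in 12.1 collect.

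**Cost.** Slightly longer surveys, some non-COVID reports to sort, and a consent-text change, since a third party would be giving medical information. Section 12.1 limits collection to data needed for the objectives. Admissions fall within objective 1 as written; the back-up questions should stay limited to the items above. The survey change comes first; the back-up contact is secondary.

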#### **8.4.16 Interview with subject for Healthcare Resource Utilization (HRU) and Adverse device effect (ADE) reporting**

In the case of a hospital episode or ADE as reported by the subject, qualified medical health professionals will contact the subject directly by phone and obtain relevant information through a structured interview. Data on HRU and ADEs will be entered directly into the eCRF system. Additionally, the clinical team will report all ADEs and device deficiencies to the Ava bracelet manufacturers within 5 business days of notification from the subject. All potential or probably serious adverse device effects (SADEs) are to be reported by the clinical team to the device manufacturer within 24 hours of notification from the subject.

#### **8.4.17 Return of Ava bracelet**

At the end of the study, subjects will be instructed on how to return the Ava bracelet and any other relevant study materials to the study team.

[figure not shown]

Figure 4: COVID-RED subject journey. Red shapes correspond to potential exclusion, dropout or missing information; green shapes correspond to protocol adherence.

